## Abstract

**Background:**

Several heart failure studies have shown promising results for implementing telehealthcare. These studies have led to clinical and political interest in telehealthcare as a way to improve heart failure outcomes and lower costs. However, there is a need for large-scale clinical trials with cost-effectiveness assessments.

**Methods/design:**

The present study is known as the TeleCare North Heart Failure Trial in Denmark. We are studying the health effectiveness and cost-effectiveness of a telehealth (Telekit) solution compared with usual care for patients with heart failure. The design is a multicenter, two-arm, parallel-group, nonblinded, superiority randomized controlled trial. Outpatient healthcare centers will be responsible for recruiting eligible participants (600 participants are expected) for the trial in the geographic area of the North Denmark Region. Participants are qualified for inclusion if they have been diagnosed according to national guidelines and are categorized in New York Heart Association class 2, 3, or 4. Patients must have a permanent residence and be motivated to use telehealth care. The primary outcomes are changes in health-related quality of life (assessed using the Kansas City Cardiomyopathy Questionnaire, the EuroQol EQ-5D-5L questionnaire, and the Short Form Health Survey [SF-36]) and in the incremental cost-effectiveness ratio measured from baseline to follow-up. The secondary outcomes are changes in mortality and in physiological indicators such as blood pressure, pulse, and weight.

**Discussion:**

The TeleCare North Heart Failure Trial is intended to improve the international evidence base for the health effectiveness and cost-effectiveness of telehealthcare for patients with heart failure. The expectation is that the results of the trial can be generalized to all municipalities in Denmark and serve as an inspiration for further international research.

**Trial registration:**

ClinicalTrials.gov (NCT02860013). Registered on 28 July 2016.

**Electronic supplementary material:**

The online version of this article (doi:10.1186/s13063-016-1722-5) contains supplementary material, which is available to authorized users.

## Background

Heart failure (HF) is a condition in which the heart muscle is weakened and is therefore unable to pump blood sufficiently through the body [1, 2]. HF often develops after other conditions have damaged the heart. Some of the common causes of HF are coronary heart disease, diabetes, and high blood pressure. Approximately 26 million people worldwide are living with HF [3]. In many countries, population-based studies have found that approximately 1–2% of people have HF [4–6]. The prognosis for these patients is not good, with survival rates worse than those for many types of cancer. Moreover, HF induces great stress on patients, caregivers, and health systems. Demands on healthcare services are expected to increase greatly in the coming years as the number of patient diagnoses rise because of aging populations and damaging lifestyles. HF costs an estimated $20 billion each year in the United States [7]. This total cost includes the cost of medications to treat HF and the cost of healthcare services [1, 2].

Approximately 60,000–100,000 people in Denmark have HF, and the incidence of HF is increasing [8]. Moreover, there are approximately 11,000 hospitalizations per year for HF in Denmark [8]. The average age of patients with HF is 72 years, and the incidence increases with age. Approximately 5% of people over 75 have HF, and the proportion rises to over 10% for people over 85 years of age.

The prevention of HF-related disease and death needs to be made a worldwide healthcare priority [1, 2]. Despite the increasing number of people living with and dying as a result of HF, awareness of HF is low among the public, politicians, and some health professionals. Although there is no cure for HF, many cases are preventable, and most patients can be treated successfully to improve their quality of life and survival rate.

Studies of telehealthcare show positive results regarding health outcomes and quality of life in other patients with chronic illness [9]. Some studies of feasibility indicate that the use of telehealthcare may also lower the costs of healthcare [10–13]. Additionally, several studies have shown promising results for telehealthcare with regard to HF [14, 15], whereas others have not found an effect [16, 17]. These studies have led to increased political and clinical attention to telehealthcare as a means of improving outcomes for patients with HF and lowering costs. However, there is a need for large-scale clinical trials with cost-effectiveness assessments in telehealthcare research [14].

In Denmark, healthcare decision makers have agreed to support the advancement of research into the health effectiveness and cost-effectiveness of telehealthcare for patients with HF. As part of the national Danish plan for the dissemination of telemedicine, a full-scale randomized trial has been planned for the North Denmark Region (Region Nordjylland). The North Denmark Region is one of five regions in Denmark and has healthcare responsibility for approximately 580,000 people. The project is based on experiences with and solutions arising from the TeleCare North COPD trial [18]. The results of the trial will inform political and clinical decisions regarding how to implement a telehealthcare solution as a national standard for HF healthcare in Denmark.

The aims of this trial are separated into two focus areas. The first area aims to evaluate whether a specific telehealth solution that is serving as a supplement to usual healthcare increases quality of life for patients with HF compared with the quality of life of those receiving usual healthcare alone. The second area aims to evaluate the cost-effectiveness of this specific telehealth solution.

## Methods/design

### Study design

This trial, the TeleCare North Heart Failure Trial in Denmark, runs from 2016 to December 2017. It is a full-scale randomized trial with approximately 12 months of follow-up conducted throughout the whole North Denmark Region (Fig. 1). All results will be published in international journals at the end of the trial. (See Additional file 1 for information regarding the Standard Protocol Items: Recommendations for Interventional Trials [SPIRIT] checklist and Additional file 2 for the SPIRIT figure.)

**Fig. 1 Fig1:**
[figure not shown]
Flow diagram for inclusion, treatment, and follow-up

### Participants

#### Inclusion criteria

All patients with HF who may benefit from telehealthcare are eligible for inclusion. Participants are qualified for inclusion if they have been diagnosed with HF according to national guidelines [19] and are categorized in New York Heart Association class 2, 3, or 4. Patients must have a permanent residence and be motivated to use telehealthcare. Motivation is simply assessed by the healthcare personnel by asking the patient prior to inclusion. Moreover, patients must have a landline or mobile phone, and they must be able to speak Danish or live with a relative who speaks Danish. In the latter case, the relative must be able to help the patient by translating information regarding the use of telehealthcare.

#### Exclusion criteria

Exclusion criteria are patients without a landline phone, a mobile phone, or GSM (global system for mobile communications) coverage; patients not able to understand Danish adequately to complete the questionnaires in the study. Comorbidity is not an exclusion criterion.

### Recruitment

Recruitment takes place in three outpatient healthcare centers in the North Denmark Region (Aalborg University Hospital, Vendsyssel Hospital, and Thy-Mors Hospital). The recruitment includes both newly diagnosed patients and people with an existing diagnosis of HF. For pragmatic reasons, recruitment will be consecutive; that is, the first patients recruited in the project will receive the intervention for a longer time span than those included later in the process. Clinic staff will be responsible for identifying potential participants and assessing eligibility when participants are in contact with the outpatient healthcare center for other reasons. The clinical staff are responsible for telling the patient about the trial, and a printed folder with information is handed to the patient. All relevant clinical staff have been informed in meetings by the trial administration and have been supplied with written information about how to identify potential participants and how to include them.

The outpatient healthcare centers will send signed informed consent forms, together with the patient questionnaires and baseline physical measurements, to the trial administrators. The patient questionnaires include questions about the participants’ baseline health-related quality of life (Kansas City Cardiomyopathy Questionnaire [KCCQ], EuroQol EQ-5D-5L questionnaire, and Short Form Health Survey [SF-36]) and demographic characteristics (age, sex, education level, comorbidities, smoking habits, marital status, and job status). The patient questionnaires are completed at the outpatient healthcare center before each patient is assigned to the telehealthcare (intervention) group or usual healthcare (control) group. If the patient feels more confident in answering the questionnaire at home, this will be possible. All primary outcome data will be entered electronically. Original study forms will be entered and kept on file.

### Randomization

The randomization of patients to either telehealthcare (intervention) or usual healthcare (control) is performed at the outpatient center after the patients have signed informed consent forms. Patient assignments are made using prepacked bundles of ten envelopes, each with a card, with assignment of five patients to the intervention group and five to the control group. Each prepacked bundle of ten envelopes is shuffled. In the outpatient healthcare center, a prepacked bundle is chosen to be the active bundle (i.e., the bundle used for assigning patients at random). When three envelopes are left in an active bundle, they are shuffled into a new bundle, and this new bundle is used as the active bundle.

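### Envelopes are re-mixed by hand at the outpatient center during recruitment, so no allocation order exists in advance to audit against and the described procedure does not secure concealment

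*Protocol article*

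**What the plan says.** All of the procedure is in the Randomization section of the protocol article.

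- **Place and time.** Randomization "is performed at the outpatient center after the patients have signed informed consent forms".
- **Device.** "Patient assignments are made using prepacked bundles of ten envelopes, each with a card, with assignment of five patients to the intervention group", and the other five to control. "Each prepacked bundle of ten envelopes is shuffled".
- **Choice of bundle.** "In the outpatient healthcare center, a prepacked bundle is chosen to be the active bundle". No order of bundles is given.
- **Carry-over.** "When three envelopes are left in an active bundle, they are shuffled into a new bundle", and the enlarged bundle then becomes the active one.

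The section uses the passive voice throughout. It names nobody as shuffling, choosing or opening, and it neither states nor denies sealing, opacity, numbering or a log.

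The setting is described elsewhere in the article. The abstract calls the study a "nonblinded, superiority randomized controlled trial". Under Recruitment, "Clinic staff will be responsible for identifying potential participants and assessing eligibility". Under Inclusion criteria, "Motivation is simply assessed by the healthcare personnel by asking the patient prior to inclusion". Under Outcome assessments (Effectiveness), the primary outcome is the change in SF-36 and KCCQ, both completed by the patient.

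**The concern.** Concealment normally rests on an order that is fixed before the patient arrives and is out of reach of whoever decides on entry. A sequence of that kind also serves as the reference against which each allocation can later be verified. Here the physical order is remade at the place of recruitment each time a bundle runs down to three envelopes.

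The setting makes this matter. Eligibility includes a judgment of motivation, arms are known once assigned, and the outcome is the patient's own report. If the next arm could influence who is entered or when, the arms would differ in prognosis and the SF-36 difference would carry that gap. The Discussion says the result may support a national standard for telehealthcare, so a challenge to the allocation would be costly to leave unanswered.

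**Working it through.** **1. Can a prepared order survive the stated rule?** A bundle starts with 10 envelopes and seven are used. The remaining 3 are mixed with 10 new ones, giving a pool of 13, which is shuffled. Ten are then used before the next mixing. Envelopes numbered in sequence would lose their order at each mixing, and the active bundle is itself picked without a stated order. A log could record which card was used, but not whether it was the card due. This follows from the stated text and does not depend on whether envelopes are sealed or opaque.

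**2. How predictable is the next card?** I simulated the written rule and, for comparison, strict blocks of ten, for an observer who knows the rule and every earlier allocation at the center. I used one stream of 316 patients and, separately, 105 patients per center.

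| Scheme | Best guess correct | Allocation certain |
|---|---|---|
| Strict blocks of ten | 65% | 16% |
| Written carry-over rule | 60% | 1% |

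Both stream lengths give these values to the nearest point. The carry-over makes guessing harder. Any blocked scheme exceeds 50% for an observer who knows the earlier allocations.

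**3. The plan's own figure.** Inputs from Sample size: difference 5, SD 15, power 80%, two-sided 0.05, equal groups, 10% loss.

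- n per arm = 2 × (1.960 + 0.842)² × 15² / 5² = 141.3, so 142 per arm and 284 in total.
- 284 / 0.90 = 315.6, so 316.

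Both stated figures reproduce and are not disputed.

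**4. What steering would do, by assumption only.** Suppose a share f of patients is allocated by prognosis, the better half to one arm and the poorer half to the other, and the two halves differ by g points in expected change. All other patients are allocated at random. The expected difference between arms with no treatment effect is then bias = f × g. Neither f nor g is in the document.

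| f | g = 5 | g = 10 |
|---|---|---|
| 0% | 0 | 0 |
| 5% | 0.25 | 0.5 |
| 10% | 0.5 | 1.0 |
| 20% | 1.0 | 2.0 |

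With 142 per arm, SE = 15 × √(2/142) = 1.78. The two-sided type I error is 1 − Φ(1.96 − bias/SE) + Φ(−1.96 − bias/SE):

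| Bias (points) | Bias/SE | Type I error |
|---|---|---|
| 0 | 0 | 5.0% |
| 0.25 | 0.14 | 5.2% |
| 0.5 | 0.28 | 5.9% |
| 1.0 | 0.56 | 8.7% |
| 2.0 | 1.12 | 20.2% |

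At the roughly 600 participants expected in the abstract, the SE is smaller and the same bias would weigh more.

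**The case against.** The strongest reply has four parts.

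- **Nobody is named.** A reader might infer that the recruiting staff shuffle and re-mix the envelopes. The text does not say so, and the initial shuffle of prepacked bundles may take place before delivery. This stands. What remains is that randomization is placed at the center and nothing described separates the envelopes from those who recruit.
- **Undetected steering needs more than the text gives.** A reader might infer that a card could be opened and put back unnoticed, leaving the 5:5 totals intact. That requires envelopes that are unsealed or can be resealed, and no log. An article may leave such details to the full protocol, so their absence is not a finding and the inference is not supported. The lack of a prepared order stands regardless.
- **The rule lowers predictability.** A reader might take a 60% guess rate as the harm. It is lower than for strict blocks of ten, and a remedy that keeps the same rule would not lower it. This stands in full, and no bias from guessing is claimed.
- **The analysis offers some protection.** Recruitment has questionnaires completed before assignment, the outcome is change from baseline, and Statistical methods allows adjustment for baseline differences. A claim that selection could never be detected or removed would therefore be too strong. These safeguards cover only measured differences, however. Recruitment also lets patients answer at home without saying that assignment waits for the form.

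**Conclusion.** The point holds in limited form. The stated procedure leaves no allocation order fixed in advance, so allocations cannot be audited against one. In a nonblinded trial with a subjective entry criterion and self-reported outcomes, concealment is not secured by what is described, and selection on unmeasured prognosis could not be reliably excluded afterwards.

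This is a weakness of method, with no measured bias behind it. The range of 0 to 2 points, and of 5% to about 20% type I error at 284 patients with SD 15, rests wholly on assumed f of 0 to 20% and g of 5 to 10 points, and it begins at no effect. Nothing in the document shows that any allocation was steered. The sample size is unaffected. The change is worth making because a better method is cheap and Trial status says that recruitment is ongoing.

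**What to change.** For patients still to be recruited:

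- Replace choosing, shuffling and carrying over envelopes at the center with one computer-generated list per center, prepared in advance and held by the trial administrators. The program can reproduce the ten-envelope, three-left rule, so predictability does not rise. It does not fall either: the guess rate stays at about 60% for someone who knows all earlier allocations.
- Release each allocation by telephone or web. Alternatively, supply consecutively numbered, sealed, opaque envelopes, opened strictly in order.
- Allocate only after consent and the baseline questionnaire are complete, including when the form is filled in at home. Log patient ID, date and time.
- Record the date of the change, and report baseline SF-36 by arm before and after it, as a partial check on patients already randomized.
- State who handled the envelopes under the old method.

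The cost is a short amendment and some hours of preparation by administrators who already receive the consent forms and baseline data. The downside is that two allocation methods must be reported, since patients already randomized keep the old one.

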### Intervention

#### Telekit

The telehealthcare solution, Telekit, is a tablet (Samsung Galaxy Tab 2; Samsung, Seoul, South Korea) that can be used to collect data from various external devices and disease-specific questionnaires. In the present study, the external devices will collect disease-specific data (blood pressure, pulse, and weight) from two devices and wirelessly transmit this data and the data from questionnaires to the central clinical system. The two external devices are a digital blood pressure monitor (Model UA-767 Plus BT-C; A&D Medical, Tokyo, Japan) and a scale (Precision Health Scale, UC-321PBT-C; A&D Medical). The software for the tablet, including the framework for the disease-specific questionnaires, was developed by Silverbullet (Aarhus, Denmark; www.opentele.silverbullet.dk). The questionnaires were constructed by clinical domain experts in the North Denmark Region. The tablet actively reminds the patients when it is time to take measurements and answer questionnaires. The patients, their relatives, and general practitioners can access the collected data via a public website (https://www.sundhed.dk/).

#### Starting the intervention

After randomization, patients with HF in the intervention group will be contacted (via telephone) by their municipality. The Telekit (including external devices) is ordered through Atea (Atea Danmark, Aalborg, Denmark), which delivers and installs the Telekit at home with the citizen. A nurse from the HF patient’s municipality will instruct the patient in the use of the Telekit. The municipality nurse will show the patient how to use the tablet and how to take physical measurements and will guide the patient through the Telekit manual before letting the patient try the Telekit him- or herself. Patients will be asked to use the scale and blood pressure monitor daily during the first 2 weeks and one to two times weekly after the first 2 weeks. A follow-up visit is scheduled between 2 and 4 weeks after the first appointment to ensure that the patient uses the Telekit properly.

### Measurement assessment

The data, which include measurements (blood pressure, pulse, and weight) and symptom-specific information from the tablet questionnaire will be assessed by a specially trained nurse. The responsibility is shared between the municipalities and the outpatient healthcare centers, depending on where the patients are affiliated.

Data assessment implies that the patient’s data are seen, interpreted, and evaluated to determine whether there should be an intervention. The data assessments will be conducted at fixed intervals (typically one or two times per week). After each assessment, an acknowledgement will be sent to the patient. If a patient’s measurements are not received as expected, the patient will be contacted. The measurements are classified as being within the normal range or outside the normal range. These predefined thresholds are adjusted if necessary during the first 14 days of measurements to fit the individual patient. The predefined thresholds are systolic blood pressure 170–100 mmHg, diastolic blood pressure 90–50 mmHg, pulse 80–55 beats/minute, and weight ±2 kg.

If the clinician observes abnormal measurements, several options are available:The clinician can contact the patient and ask for a new measurement if the measurement is considered to be less suitable.The clinician can contact the patient to assess the patients condition.It is possible to start a self-treatment plan for the patient.If the clinician judges that the patient is cable of taking contact to his or her own general practitioner, the patient is asked to do so.The clinician can contact the patient’s general practitioner directly.

The intervention needed is always a clinical judgment based on the patient’s measurement and possibly a subsequently contact with the patient. It should be noted that the goal is to help the patient understand his or her own data and thereby empower the patient to take responsibility for handling the disease.

### Outcome assessments

#### Effectiveness

All outcome measures for the two groups (usual care group and the intervention group) are collected at baseline and follow-up. The primary outcome is change in health-related quality of life (SF-36 and KCCQ) from baseline to follow-up. SF-36 total score is used as the primary outcome, and the subscales are used as secondary outcomes. The secondary outcomes for effectiveness are changes in the mortality rate and physiological measurements such as blood pressure, pulse, and weight from baseline to follow-up. Mortality rate is considered only if enough participants are included to satisfy the power calculation for this secondary outcome. The clinical impact of telehealthcare is considered to be positive if no increase in mortality is observed and if pulse and blood pressure are lowered.

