#### Cost assessment

The main outcome for cost is the incremental cost-effectiveness ratio (ICER). The ICER is measured as the total cost per quality-adjusted life-year (QALY) gained from baseline to follow-up. It is anticipated that telehealthcare will increase the participants’ quality of life, but no difference in mortality is expected. Additionally, it is expected that telehealthcare will reduce cost, particularly due to a reduction in the number of admissions/readmissions and outpatient visits [20].

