### Sample size

A sample size calculation for effectiveness was performed using OpenEpi (http://www.openepi.com/Menu/OE_Menu.htm). Conservative estimates were applied for the minimal clinically important difference (change equal to 5 for the SF-36 physical component summary). With a power of 80%, groups of equal size, a standard deviation of 15, and a two-sided *p* value of <0.05, the required sample size is estimated to be at least 284 participants. With an expected loss to follow-up of 10%, the total required sample size is estimated to be at least 316 participants.

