#### Effectiveness

To evaluate effectiveness, differences between the intervention group and the control group with regard to SF-36 scores, mortality rates, and physical measurements from baseline to follow-up will be analyzed. The outcome will primarily be analyzed using two-sample paired statistics (e.g., two-sample paired *t* test), such that the differences from baseline to follow-up will be assessed between groups.

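### The primary effectiveness outcome is stated inconsistently, and the sample size is calculated for a score (the SF-36 physical component summary) that no section declares primary

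*Protocol article*

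**What the plan says.** Five places in the protocol article bear on the primary outcome.

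- **Abstract, Methods/design.** Several primaries are listed: "The primary outcomes are changes in health-related quality of life (assessed using the Kansas City Cardiomyopathy Questionnaire, the EuroQol EQ-5D-5L questionnaire", then SF-36, "and in the incremental cost-effectiveness ratio measured from baseline to follow-up".
- **Outcome assessments, Effectiveness.** One sentence reads: "The primary outcome is change in health-related quality of life (SF-36 and KCCQ) from baseline to follow-up". The next reads: "SF-36 total score is used as the primary outcome, and the subscales are used as secondary outcomes". The secondary effectiveness outcomes named after that are mortality and physiological measurements. KCCQ is not among them.
- **Outcome assessments, Cost assessment.** "The main outcome for cost is the incremental cost-effectiveness ratio (ICER"). It is not called primary here.
- **Sample size.** "Conservative estimates were applied for the minimal clinically important difference (change equal to 5 for the SF-36 physical component summary"), with SD 15, 80% power, two-sided 0.05 and equal groups. This gives at least 284 participants, or at least 316 allowing for 10% loss to follow-up.
- **Statistical methods, Effectiveness.** The analysis covers "differences between the intervention group and the control group with regard to SF-36 scores, mortality rates, and physical measurements". No SF-36 score is singled out, and KCCQ does not appear.

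The abstract also says that 600 participants are expected.

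**The concern.** A protocol should let a reader identify, before any results exist, the one comparison on which the effectiveness claim rests. Here the candidates are an SF-36 total score, KCCQ, and the PCS as the score actually used for sizing. Each has some support in the text.

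This matters more than usual because the trial is nonblinded, the instruments are patient-reported, and the Background and Discussion say the results will inform a national standard. After the results are seen, more than one score could be presented as the prespecified primary, with a sentence in the article to support it.

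The power statement is also detached from its target. Power of 80% is a property of one test on one score with a given difference and SD. The article gives those inputs only for the PCS.

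**Working it through.** **1. Reproduce the stated sample size.** Inputs from the Sample size section: difference 5, SD 15, two-sided 0.05 (z = 1.96), power 80% (z = 0.8416), 1:1 allocation.

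- n per arm = 2 × (1.96 + 0.8416)² × 15² / 5² = 2 × 7.849 × 9 = 141.3, so 142 per arm and 284 in total.
- Power at 142 per arm: 5 / (15 × √(2/142)) = 2.809; 2.809 − 1.96 = 0.849; power = 80.2%.
- Loss to follow-up: 284 / 0.90 = 315.6, so 316.

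Both figures match. The arithmetic is right for a single test on the PCS.

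**2. Compare the score that was sized with the scores declared primary.**

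| Section | Score(s) given |
|---|---|
| Abstract | KCCQ, EQ-5D-5L, SF-36, ICER (all primary) |
| Outcome assessments, first statement | SF-36 and KCCQ (primary) |
| Outcome assessments, second statement | SF-36 total score (primary) |
| Sample size | SF-36 PCS |
| Effectiveness analysis | SF-36 scores, unspecified; no KCCQ |

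The PCS appears only in the Sample size row. If component summaries are counted among the SF-36 subscales, the PCS would even be secondary. No difference or SD is given for the SF-36 total, KCCQ or EQ-5D-5L.

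**3. Error rate if either quality-of-life instrument could carry the claim.** Assume two tests, each unadjusted at two-sided 0.05, with success on either.

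- Independent: 1 − 0.95² = 9.75%.
- Correlation 0.5 (simulated bivariate normal): 9.0%.
- Correlation 0.7: 8.4%.

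The range is about 8 to 10%. The correlations are assumptions.

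**4. Power if the SF-36 total is the primary score.** This cannot be computed from the article. As an illustration, assume a 5-point difference and a range of SDs. Power = Φ(5 / (SD × √(2/n)) − 1.96), with n per arm. The last column takes the expected 600 with 10% loss: 600 × 0.90 = 540, or 270 per arm.

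| Assumed SD | Evaluable needed for 80% | Power at 284 evaluable | Power at 540 evaluable |
|---|---|---|---|
| 10 | 126 | 99% | above 99% |
| 15 | 284 | 80% | 97% |
| 20 | 504 | 56% | 83% |
| 25 | 786 | 39% | 64% |

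The SD 15 row is also the PCS calculation.

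**The case against.** **The second sentence in the outcome section settles it.** It can fairly be read as narrowing the sentence before it, so the two need not contradict each other. On that reading there is one declared primary, the SF-36 total. But KCCQ is then left without a status: it is not an SF-36 subscale, is not listed as secondary, and is absent from the analysis. The abstract still disagrees, and the sample size still concerns another score.

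**EQ-5D-5L and the ICER belong to the economic aim.** This stands. The Background separates the two aims, and the Cost assessment text under Statistical methods uses EQ-5D-5L for QALYs and reports the ICER through bootstrapping, Monte Carlo simulation and an acceptability curve. No significance test is planned for either. A reader might count all four outcomes in the abstract and infer a familywise error of 13 to 19%. The document does not support that, because two of the four spend no alpha. What remains is that the abstract labels them primary alongside the clinical instruments.

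**Recruitment well above 316 is expected.** This also stands. A reader might infer from the 56% at SD 20 that the trial is underpowered. At the expected 600 the same assumption gives 83%, and the stated sample size is only a minimum. A shortfall appears only with a larger assumed SD or if recruitment stops near 316. Extra patients do not, however, settle which score decides the trial, nor do they lower a familywise error.

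**Multiplicity rules and SF-36 scoring may be in the analysis plan.** Agreed. That plan is not shown, so the absence here of an alpha hierarchy, or of a rule for forming an SF-36 total, is not a finding. An analysis plan cannot, though, make the sections of this article agree with one another.

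**Conclusion.** The point holds as an inconsistency in the declared primary effectiveness outcome, together with a sample size tied to a score that no section declares primary. The calculation itself is correct (284 and 316 reproduce exactly), but its 80% power and two-sided 5% error apply to one test on the PCS and to no declared primary outcome.

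The size of the error problem is about 8 to 10% instead of 5%. This applies only if either SF-36 or KCCQ could carry the claim without adjustment, with correlation between 0.7 and 0. The article does not state such a rule, so this is what the ambiguity permits and not what is planned.

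The effect on power is unknown. For an SF-36 total it depends on a difference and SD that the article does not give. The illustrations run from 39% to 99% at 284 evaluable, and from 64% to above 99% at 540. An inadequate sample size is therefore not shown. The main cost is that the deciding score stays open in a nonblinded trial with patient-reported outcomes.

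**What to change.** Before analysis, name one primary effectiveness score in identical words in the Abstract, Outcome assessments, Sample size and Statistical methods, and base the sample-size difference and SD on that score. Either route is sound:

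- Declare the SF-36 PCS primary, since it is the only score with stated inputs, and drop the SF-36 total score as primary. The figures 284 and 316 then stand.
- Keep the SF-36 total (or choose KCCQ) as primary, and restate the difference, SD, sample size and power for that score.

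In either case, make the other instrument explicitly secondary and include KCCQ in the effectiveness analysis. In the abstract, label the ICER (with EQ-5D-5L supplying the QALYs) as the separate economic outcome, as the two Cost assessment sections already treat it.

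The cost is a wording change, with a recalculation under the second route. No extra data collection is needed. The sponsor gives up the freedom to choose among instruments once results are known, and the stated power may change if a score other than the PCS is kept.
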